## Abstract

Individuals who suffer from depressive symptoms experience a substantial impact on psychosocial functioning, physical health, mortality, and quality of life. In the search for therapeutic strategies, exercise has been found to play a relevant part in its treatment. However, the promotion of exercise entails adherence difficulties that arose out of the tendency towards sedentarism led by symptomatology. Personalised exercise plans on top of usual care have the potential to enhance behavioural changes and mental health. The present study aims at evaluating the changes in functioning deriving from a blended intervention merging a psychological intervention with a personalised exercise programme based on medical assessment. We will conduct a three-arm randomised controlled trial in which 172 participants suffering from mild–moderate depressive symptoms will be allocated to Intervention A (personalised exercise group programme + app with motivational messages), B (personalised exercise group programme + app with no motivational messages) or control group (app with no motivational messages). Data regarding global functioning, well-being, symptoms, physical activity, and exercise capacity will be collected at baseline, 4, 12, and 36 weeks. The results of this trial will provide information about whether this physical activity support programme may be efficient for improving mental and physical health outcomes. Trial registration: ClinicalTrials.gov NCT04857944 (accessed on 15 April 2021). Registered April 2021.

## 1. Introduction

Major depressive disorder (MDD) was reported as the third leading cause of years lived with disability in the world and the third leading cause in the areas with the highest sociodemographic index by the Global Burden of Disease [1]. Individuals presenting depressive symptomatology experience, regardless of their diagnoses, a significant impact on social and work functioning, physical health and mortality.

Moreover, despite the wide range of effective treatments licensed for depression, MDD is the first worldwide leading cause of impairment and it is globally suffered by over 300 million people [2]. This is partly due to undertreatment being the rule rather than the exception for depressed patients. In high-income countries, only one in five depressed individuals receives systematically minimally adequate treatment [3].

A symptom-based, dimensional view of mental health disorders has the practical advantage of genuinely respecting individual differences. By lacking rigid nosotaxis, professionals are free to enrich each patient clinical case description and their derived needs. One-size-fits-all categorical descriptions lead too often to guideline/algorithm diagnostic-driven therapeutic recommendations which most of the time may not cover patient needs and will not consider patient-already-existing capabilities. In other words, diagnostic-driven treatment algorithms too often become a Procrustes bed: nobody ever fits therapeutic recommendations, which usually end up becoming impractical.

Conversely, the very intrinsic nature of symptom-based approaches—per se respecting individual differences—enhances personalised medicine. The symptom-based mental-health paradigm becomes, by definition, transdiagnostic, a word that describes most daily clinical jobs. The path to precision medicine in mental health is being built and various transdiagnostic treatment programmes for affective disorders are being designed [4,5].

A solid body of scientific evidence supports the regular practise of exercise and validates the many benefits it brings for people with mental disorders, among which are the reductions of depressive symptoms, a positive anxiolytic effect and better quality of life [6]. In support of this, structured and limited in time exercise programmes are particularly recommended as treatments for people with mild to moderate depression or with persistent subthreshold depressive symptoms [7].

However, the effective promotion of this lifestyle entails a challenge, essentially due to adherence difficulties arising out of the tendency towards sedentarism usually led by symptomatology (apathy, fatigue, low motivation, anxiety, etc.). People with MDD engage in high levels of sedentary behaviour and low levels of physical activity [8], which are predictors of mortality. Moreover, higher levels of symptoms of anxiety are associated with higher levels of sedentary behaviour [9].

Here, special consideration must be given to what seems the most important factor associated with the performance of regular exercise among the population suffering from mood disorders: the delivery of advice or indications by health professionals [10]. Personalised medicine stresses a practical need for transdisciplinary effort.

Physical Medicine and Rehabilitation Therapy can have a positive impact on patients with depressive symptoms. Specialists in this field are uniquely positioned to evaluate a patient’s current physical capabilities and limitations, design and discuss a personalised treatment plan and prescribe tailored exercise routines to effectively cope with depressive symptoms in a realistic approach.

Group exercise sessions have specifically shown great benefits [11], and beyond physiological changes and the regulation of sleep produced by physical activity per se, this modality represents added value as it boosts social contact, mirroring, interaction and facilitates the support of other people. Furthermore, the implementation of group interventions is proposed as an alternative to maximizing the optimisation of the use of available resources and services.

A multidisciplinary-based approach merging Physical Medicine and Rehabilitation care with psychological interventions focusing on needs and capabilities, and tailored exercise routines should have an impact on motivation to increase physical activity—including both aerobic and anaerobic exercises—and enhance behavioural changes towards a healthier lifestyle.

We hypothesized that participation in a brief app-blended group intervention promoting personalised exercise and activity, as an add-on to treatment-as-usual, will improve functioning and well-being. Both efficacy measures would result in a lesser impact of depressive symptomatology in life.

The main objective of this research is to evaluate the changes in functioning deriving from a blended intervention merging psychological intervention aimed at increasing activity and exercise with a personalised exercise programme based on medical assessment on subjects suffering from mild to moderate depressive symptoms.

## 2. Materials and Methods

### 2.1. Study Design

We will conduct a 3-arm randomised controlled clinical trial in which 172 eligible participants will be allocated to one of the following conditions:Intervention A (*N* = 48): Personalised exercise group programme + smart band + IDEApp (Mass Factory Urban Accessible Mobility S.L, Barcelona, Spain) with motivational messages: After study entry and baseline assessments, subjects will attend the one-month IDEA group sessions aimed at promoting physical activity and exercise. Participants randomly assigned to this study arm will use the smart band and IDEApp with the motivation set enabled, allowing participants to receive the messages according to their compliance and adherence to the personalised prescriptions. After group sessions, study subjects will start receiving the messages in Week 4, and up until the end of the trial. Intervention A study subjects will be expected to continue using the smart band and IDEApp for 8 consecutive months.Intervention B (*N* = 48): Personalised exercise group programme + smart band + IDEApp without motivational messages: Subjects will follow the same procedure as Intervention A, with the difference that the IDEApp will have the motivation set disabled and therefore will not receive any messages regarding their compliance. After group sessions, study subjects will be expected to continue using the smart band and IDEApp for 8 consecutive months.Control Group (*N* = 76): smart band + IDEApp without motivational messages: After study entry and baseline assessments, all patients assigned to the control group will receive both the IDEApp and the smart band, but the motivation set will be disabled. Study subjects will be expected to use the smart band and IDEApp for 8 consecutive months.

All participants, regardless of their treatment condition, will be read a short text about the benefits of regular exercise on mood during the initial clinical interview, in order to make sure that they have listened to this unspecific advice at least once.

All participants will continue receiving naturalistic pharmacological and/or psychological treatment, without any research-related disruption. A schematic diagram including the schedule of enrolment, assessments, and visits for participants is available in Figure 1.

We hereby propose a seminal project on the efficacy of personalised exercise plans and psychological advice leading to a regular activity increase on top of the usual treatment regime of subjects presenting with depressive symptomatology: The IDEA (acronym standing for “Improving Depression through Exercise and Activity”) programme. Moreover, the proposal also introduces the advantages of e-mental health to maximise the results. The inclusion of a digital platform app format as a mobile support ‘companion’ tool and a smart band in the project has the potential to prolong motivation and exercise performance and maintain the benefits in the long term. At the same time, it allows for a non-invasive and fine-tuning measuring of variables and changes related to the activity.

### 2.2. Study Setting

The research setting will be outpatient mental health centres and General Practice surgeries belonging to the healthcare network of Parc de Salut Mar in Barcelona, Spain, which covers a catchment area of over 700,000 people for mental health. The available Gross Domestic Product of this area is below average when compared to other districts of Barcelona city. In addition, this area includes some of the neighbourhoods with the lowest incomes in the city [12].

### 2.3. Eligibility Criteria

All participants will meet the following inclusion criteria: aged 18–65 years, presenting mild to moderate depressive symptoms according to the Montgomery–Asberg Depression Rating Scale (MADRS score > 16 and <34), currently owning an Android-compatible smartphone, fluent in Spanish language, basic knowledge and skills using a smartphone, and able to provide written informed consent to participate. Potential participants will be excluded as per the following exclusion criteria: severe cognitive and/or physical impairment; cognitive deficit or developmental disorder; current psychotic, melancholic or catatonic futures; drug or alcohol dependence; modification of drug treatment (or its dose) in the last month; beginning of psychological treatment in the last month; beginning of biophysical treatment in the last month; BMI > 40; physical disability. Any general practitioner, nurse, psychologist or psychiatrist treating the patient will make the referral.

Group sessions will be facilitated by a psychologist ([name]) and a physiotherapist ([name]) with accredited experience who will receive a brief therapy training.

Before any study procedures occur, participants will be informed about the study characteristics, they will be provided with a study information leaflet and a written informed consent form must be signed by them. After signing the informed consent, an experienced (more than five years of regular clinical practise since specialisation) clinical psychologist or a psychiatrist will confirm or disregard depressive symptomatology, administer the MADRS and judge that the subjects fulfil all the inclusion criteria items and none of the exclusion criteria requirements.

### 2.4. Interventions

#### 2.4.1. Intervention Description

The main goal of the intervention is to personalise exercise prescription and enhance motivation towards being physically active. To fulfil our objectives, a collaborative team of 4 psychologists, 2 Physical Medicine and Rehabilitation specialists (one medical doctor specialised in the field and one physiotherapist), and 1 psychiatrist designed a brief group intervention—the IDEA programme.

The programme will consist of six 90 min group sessions composed of four to six participants as working with small groups facilitates the patient’s integration and allows professionals to better detect their needs. These short intervention sessions will be distributed in one month, with a frequency of once or twice a week depending on the week of the programme. Group sessions will take place in the therapy room of Centre Fòrum–Parc de Salut Mar, which provides rehabilitation, sociosanitary and mental health services. In the exercise-oriented sessions, participants will be asked to wear sports clothes to practise the individualised exercise prescription on-site and will receive an individual brochure with indications and photographs of their prescription.

For the implementation of the sessions, we created a guide for the professionals where the content of each session and its dynamics were outlined. In the case of the individualised exercise prescription, a pool of exercises was created in order to standardise the potential exercises that will be chosen individually for each participant. Table 1 presents an overview of the IDEA programme. Detailed information regarding the content of the group sessions is available in Table S1 as Supplementary Material.

The exercise prescription will be personalised in terms of intensity and amount of time. Therefore, all participants will perform four types of exercise: stretching, aerobic, strength and relaxation. We have designed three types of programmes covering low, moderate and high intensity. Participants with higher levels of sedentarism will be prescribed 45 min sessions twice a week, while participants with lower levels will do 60 min sessions three times a week.

Participants will choose the type of aerobic exercise according to their preferences and possibilities (i.e., having easy access and knowing how to perform the exercise). Options can include—but are not limited to—walking, running, water aerobics, biking or dancing.

The intensity of the aerobic exercise will be based on the maximum age-related heart rate estimated by subtracting the age of participants from 220. All participants will receive instructions on how to keep track of their heart rate. In the low and moderate intensity programmes, participants should keep their heart rate between 45 and 54% of their maximum heart rate, while participants receiving the high-intensity programme should keep a heart between 70 and 89%. Further information regarding the personalised exercise prescription is detailed in Table S2 contained in the Supplementary Material.

As a result of the COVID-19 pandemic, we are currently facing many uncertainties around this rapidly evolving situation and the governmental measures responding to it. The IDEA trial will be conducted undertaking risk assessments and adapting trial processes when necessary. The intervention will be delivered ensuring participants and professionals’ safety by following the advice of local public health authorities (e.g., mandatory use of hygienic or surgical masks, participants will be encouraged to maintain physical distance, fitness material used will not be shared during group sessions and will be properly disinfected before and after the sessions, doors will remain open and alcohol-based hand rub will be at participants’ disposal).

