### 2.6. Sample Size

Initially, we computed a sample size of 152, given a power of 0.8, an alpha level of 0.05 and inferring functioning according to clinical remission data [28]. To our knowledge, functioning as a main outcome for physical exercise in depression has not set a precedent to guide our calculations. Thus, we computed a Cohen’s d effect size of 0.5 to make estimations more reliable. An expected drop-out rate of 20% was set, which resulted according to the initial design in two arms of 76 subjects each. However, during the cocreative process of the intervention, it was discussed whether motivational messages of the app would mask the effect of the group sessions on the outcomes of the study. Therefore, it was decided to include a third study arm to assess the intervention without motivational elements triggered by the app. We increased the sample size by adding 20 participants, which will be distributed into the two experimental groups, leaving us with a sample size of 172.

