## 3. Statistical Methods

### 3.1. Statistical Methods for Primary and Secondary Outcomes

Statistical analysis will be performed using the software SPSS Statistics 25 (IBM Corp., Armonk, NY, USA). Descriptive statistics will be used to analyse the distribution of socio-demographic and clinical characteristics among groups at baseline. Continuous variables with a normal distribution will be analysed performing an ANOVA. Where the premises of normalcy are not met, the Wilcoxon test will be used. The differences between groups on the categorical and mail clinical variables will be evaluated by using a Chi-square test. Those variables that are statistically significant may be used as covariates for a logistic or linear regression study of the factors associated with the magnitude of the effect, and determine which variables are better predictors of functioning. The effect size index will be estimated in case of correlation indexes for each of the performed analyses. To analyse efficacy, we will perform intention to treat analysis. Analysis will be two-tailed and the significance set a *p* < 0.05.

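### Arms A and B are treated in session groups of four to six, but the sample size and named tests treat all participants as independent; a within-group correlation above zero would understate the standard error of (A+B) vs Control.

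*Protocol article*

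**What the plan says.** Section 2.4.1 sets the delivery format for arms A and B: "The programme will consist of six 90 min group sessions composed of four to six participants". Sections 2.1 and 2.8 allocate 48 participants to A, 48 to B and 76 to control. Controls receive the smart band and the app but no sessions. Section 2.5.1 makes (A+B) vs Control the main comparison.

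The Introduction argues for the group format partly because "it boosts social contact, mirroring, interaction and facilitates the support of other people".

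Section 2.6 gives the basis of the sample size: "Initially, we computed a sample size of 152, given a power of 0.8, an alpha level of 0.05". It adds "Thus, we computed a Cohen’s d effect size of 0.5" and 20% drop-out, which leads to two arms of 76. The 20 later participants are explained by the third arm. Neither step mentions grouping.

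Section 3.1 states: "Continuous variables with a normal distribution will be analysed performing an ANOVA". It gives Wilcoxon as the alternative where normality fails, chi-square for categorical variables, and logistic or linear regression for predictors. It also says "Analysis will be two-tailed", with significance at 0.05. No intraclass correlation, design effect, group term or cluster-robust error appears anywhere in the article.

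**The concern.** The data for the primary contrast are partially nested: 96 outcomes arise in small groups that share sessions and peers, and 76 do not. Some groups may gel and others not. If so, members of one group resemble each other, and 96 grouped participants carry less information than 96 independent ones. A test that ignores this gives intervals for (A+B) vs Control that are too narrow and a false-positive rate above 0.05. A test that allows for it has less power than a calculation based on independence suggests.

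A primary p-value just under 0.05 would be the exposed case. The protocol's own rationale for groups makes correlation plausible, so independence should not be assumed without comment.

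**Working it through.** **1. The protocol's own figure.** Inputs from Sections 2.6 and 3.1: two-sided alpha 0.05, power 0.80, d = 0.5, drop-out 20%.

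n per arm = 2 × (1.960 + 0.842)² / 0.5² = 62.8, so 63. Then 63 × 1.2 = 75.6, so 76 per arm and 152 in total. This is the stated number exactly, obtained with independent participants and a design effect of 1.

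**2. Number of groups.** 96/6 = 16 to 96/4 = 24.

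**3. Set-up for the 172 design.** After 20% loss: 96 × 0.8 = 76.8 programme and 76 × 0.8 = 60.8 control participants, SD = 1.

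- Design effect, programme arms only: DE = 1 + (m − 1) × ICC, with m = 4, 5, 6.
- True SE = √(DE/76.8 + 1/60.8).
- SE ignoring groups = √(0.01302 + 0.01645) = 0.1717.
- Actual two-sided error of the unadjusted test = 2 × [1 − Φ(1.96 / ratio)], where ratio = true SE / 0.1717.
- Power of a valid analysis: noncentral t with effective sizes 76.8/DE and 60.8, d = 0.5.

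The ICC is assumed, since the documents give none.

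**4. One case in full (m = 5, ICC 0.05).** DE = 1 + 4 × 0.05 = 1.20. True SE = √(0.01563 + 0.01645) = 0.1791. Ratio = 1.043. Error = 0.060. Effective programme n = 76.8/1.20 = 64. Power = 0.791.

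**5. Range.**

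| ICC | m | DE | SE ratio | Two-sided error | Power |
|---|---|---|---|---|---|
| 0 | any | 1.00 | 1.000 | 0.050 | 0.824 |
| 0.02 | 4 | 1.06 | 1.013 | 0.053 | 0.814 |
| 0.02 | 6 | 1.10 | 1.022 | 0.055 | 0.808 |
| 0.05 | 4 | 1.15 | 1.033 | 0.058 | 0.799 |
| 0.05 | 6 | 1.25 | 1.054 | 0.063 | 0.783 |
| 0.10 | 4 | 1.30 | 1.064 | 0.066 | 0.775 |
| 0.10 | 6 | 1.50 | 1.105 | 0.076 | 0.743 |

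The normal approximation gives power about 0.005 to 0.007 higher in each row. If loss thins groups of five to about four, the m = 4 rows apply. For a given m, the error column does not depend on the amount of loss, because both arms shrink by the same factor.

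**6. Check by simulation.** In 20,000 simulated trials per setting (77 vs 61), the unadjusted t-test rejected a true null in 0.058 to 0.065 of trials at ICC 0.05 and in 0.066 to 0.075 at ICC 0.10. This agrees with the table within simulation error of about 0.002.

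**7. Where power crosses 0.80.** Power is 0.799 at DE = 1.15. The corresponding ICC is 0.15/(m − 1): 0.05 for groups of four and 0.03 for groups of six.

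**The case against.** The strongest reply is that the harm depends on an ICC nobody has stated. A benefit of the group format is a mean effect and does not by itself show that groups differ. Section 2.4.1 also pulls the other way: a session guide, a common pool of exercises, individual prescriptions, self-chosen aerobic activity and a single venue. The sessions last one month and the last assessment is at 36 weeks, so a group effect may fade. All of this stands. It makes a small ICC credible, and at 0.02 the distortion is slight.

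A second reply is that Section 3.1 does not clearly fix the efficacy test. The ANOVA sentence follows the baseline description, the efficacy sentence says only that analysis is by intention to treat, and a separate analysis plan could add a group term. That is fair for the model. It does not reach the sample size, which the article sets and which reproduces only with a design effect of 1. Nor does any method the article names allow for grouping.

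Three stronger readings are tempting but unsupported:

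- **The groups are closed.** The text gives only their size and six sessions in a month. The point needs shared sessions, nothing more.
- **Facilitators create the clustering.** Section 2.3 describes one psychologist and one physiotherapist. An effect common to every group adds nothing to between-group variance.
- **A vs B is inflated in the same way.** Whether A and B share groups is not stated, so this cannot be said.

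**Conclusion.** The point holds in conditional form. The design is partially nested, and neither the sample size nor the named tests allow for it. Whenever the group ICC exceeds zero, the planned approach understates the standard error of (A+B) vs Control.

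The size is modest. Over assumed ICCs of 0.02 to 0.10, the understatement is about 1% to 11% and the true error runs from about 0.053 to 0.076.

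A reader might infer that the trial is underpowered. The documents do not support that as a fact. Ignoring groups, the 172 design has power of about 0.82, so the 20 added participants absorb part of any loss although they were added for another reason. Power drops below the stated 0.80 only from an ICC of about 0.03 to 0.05, depending on group size, and noticeably only near 0.10. Nor can it be said outright that the error rate exceeds 0.05, because that requires an ICC above zero, which is plausible here but not shown.

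The result rests on the assumed ICCs, 20% loss in both arms, d = 0.5 and equal unit variances.

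**What to change.** Record a session-group identifier for every participant in A and B, from the first group onwards. Analyse (A+B) vs Control with a partially nested mixed model: a random intercept for session group in the programme arms only, each control as its own unit, and Satterthwaite degrees of freedom. The MIXED procedure in the named SPSS software can fit this. Specify that the term stays in the model whatever its estimated size.

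Restate the power of the 172 design over a range of assumed ICCs such as 0.02 to 0.10. More participants are not needed for this.

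The cost is one recorded variable and one model term. Intervals will be slightly wider, and the stated power may fall slightly below 0.80. The term cannot remove a facilitator effect common to all groups, so that should be acknowledged as part of what the comparison estimates.
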